### Participants

This study targets adults in the general Belgian population. The following inclusion criteria will be taken into account: (1) being ≥ 18 years old, (2) Dutch-speaking, (3) having Internet access and (4) being the owner of a smartphone. Before entering the study, people have to complete the ‘Physical Activity Readiness Questionnaire’ (PAR-Q) [57] which is a screening instrument to detect individuals at risk for adverse effects when being more physically active. The PAR-Q is a self-report instrument consisting of seven items to be answered by ‘yes’ or ‘no’. Participants will be excluded when one item or more will be endorsed. Participants receiving concomitant care or other interventions will not be excluded.

A convenience sample will be attained by recruiting possible participants in the city library of Ghent (i.e. ‘De Krook’), in city halls and shopping malls. Also participants will be recruited by social media, contacting participants of previous studies who indicated as having interest in other research, recruiting acquaintances and students, and applying snowball sampling.

Based on the meta-analysis of Conn et al. (2011) [58], we would like to be able to observe a small effect size of 0.19. To detect within- and between-subjects effects under significance level alpha = 0.05, and with a power of 0.80, a sample of 260 participants is needed. However, we will aim to recruit approximately 480 participants to take attrition into account. As such, an attrition rate of 46% of the participants is acceptable within this study, which seams feasible to the researchers. This is because actions to decrease drop-out were taken; no extensive questionnaires were used in MyPlan 2.0 in contrast to previous research (e.g. MyPlan 1.0) and, furthermore, the programme was adapted to increase user engagement based on both qualitative and quantitative research [46, 47].

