The participants will be randomly allocated to eight equal groups (60 participants within one group). The randomisation will be done by the author of this study. Before recruitment of participants, blocked randomisation will be used to form an allocation list for the eight different groups. A computer random number generator (http://www.randomization.com) [59] with a block size of 40 will be used to assign the group numbers in random order within each block. The allocation list will be concealed for the researcher during the recruitment of participants. Each time a participant completes a pre-test measurement (at the library, city hall, shopping mall or at home; see Fig. 4) an automatic email will be sent to the researcher. After receiving this email, the participant will be allocated to the next number on the allocation list and will consequently be assigned to a group. By doing this, the allocation will be concealed until participants are enrolled and assigned to the intervention [60]. After assignment, the researcher will not be blind for the allocated intervention: the researcher will send participants different website links to their corresponding intervention. The participants on the other hand will not be aware of the different conditions of the study: they will only receive one website link (corresponding with their intervention).

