### Data management and statistical analysis

Data management and analyses will be monitored and supervised by the team of six researchers and a PhD guidance committee. The data management plan, which describes data storage, management and confidentiality, is provided in Additional file 3. Results of the study will be published anonymously in scientific journals and via public health communication channels. For all publications, the APA guidelines for authorship eligibility will be followed.

Statistical analysis will be performed after data collection is completed. The data of our factorial randomised controlled trial will be analysed using R version 3.2.5 [73].

Descriptive statistics will be provided for the total sample and for all groups. Baseline differences between all groups regarding demographic variables, determinants of behaviour change and the level of PA and SB will be explored by using one-way analysis of variance (ANOVA) (for the continuous variables) and chi-square tests (for the nominal variables). If baseline differences occur in terms of age and gender, they will be included as a covariate factor in the analyses. We will explore the effect of other baseline differences via sensitivity analyses.

To handle our missing data, missing data mechanisms will be investigated. First, we will check whether the missing values are missing completely at random (MCAR) or missing at random (MAR) using the Little Missing Completely At Random test in R [74]. If our data are MCAR or MAR, multiple imputation will be used which provides valid results when the data are at least missing at random [75]. The analysis will be conducted in R using the MICE package [76]. However, one cannot rule out the possibility that the data will be missing not at random (MNAR), therefore sensitivity analyses will also be conducted [75].

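### Adjustment for age and gender is made to depend on baseline tests across the eight randomised groups, so chance decides the primary model's covariates and the test does not match the technique contrasts

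*Protocol article*

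**What the plan says.** All references are to the protocol article.

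- **Comparison.** Under Data management and statistical analysis: "Baseline differences between all groups regarding demographic variables, determinants of behaviour change and the level of PA and SB will be explored". The tools named are "one-way analysis of variance (ANOVA) (for the continuous variables) and chi-square tests (for the nominal variables").
- **Rule.** The next sentence reads: "If baseline differences occur in terms of age and gender, they will be included as a covariate factor in the analyses". Other baseline differences go to sensitivity analyses. No threshold is given for calling something a baseline difference.
- **Allocation.** Under Participants: "The participants will be randomly allocated to eight equal groups (60 participants within one group"). A random number generator "with a block size of 40 will be used to assign the group numbers in random order within each block". No stratification by age or sex is mentioned. Allocation follows completion of the pre-test.
- **Effects of interest.** The primary analysis is a mixed model of repeated measures within participants, for the effect of the three techniques on behaviour change. The Discussion says that the main interest is in main effects and two-way interactions.
- **Nothing overrides the rule.** No section puts age and gender in the primary model regardless of the tests. Demographic variables otherwise appear only as moderators, under the second aim.

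**The concern.** The covariates of the primary model are chosen by a test whose null hypothesis is true by design. Baseline is measured before allocation and allocation is random, so a difference between groups in age or gender is chance. The useful reason to adjust is that a variable predicts PA or SB, and the baseline test carries no information on that.

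The test is also aimed at a different target from the analysis. Seven degrees of freedom among eight groups comprise three main-effect contrasts, three two-way contrasts and one three-way contrast. The trial asks mainly about the first six, one at a time. An imbalance along one technique is diluted by six other components, so the rule will usually stay silent where adjustment would help. It can also fire on a pattern that matters for no main effect.

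At stake are precision, and the accuracy of a technique effect in trials where age or gender happens to be imbalanced on that technique.

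**Working it through.** The plan states no figure for this rule, so there is none to reproduce beyond the group sizes.

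**Inputs from the article**
- Recruitment: "we will aim to recruit approximately 480 participants to take attrition into account". 480/8 = 60 per group, as stated. Each technique is present in four groups: 4 × 60 = 240 v 240.
- Alpha 0.05 and an effect size of 0.19, both from the sample size paragraph under Participants.

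**Assumptions, not in the article**
- A baseline difference means p < 0.05. The 0.05 in the sample size paragraph is not tied to this step.
- Age and gender are independent of each other.
- The covariate-outcome correlation is 0.1, 0.3 or 0.5.

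**Step 1. How often chance triggers the rule.** One test: 5%. At least one of two: 1 − 0.95² = 0.0975, or 9.75%. Neither covariate is triggered in the remaining 90%.

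**Step 2. A realised 0.2 SD imbalance on one technique.**
- Contrast sum of squares (SD units): 480 × (0.2/2)² = 4.8.
- Tested directly on 1 df: P(χ²₁ > 4.8) = 0.028.
- The eight-group test needs χ²₇ > 14.07. The other six components must supply 14.07 − 4.8 = 9.27, and P(χ²₆ > 9.27) = 0.159.
- So the eight-group test flags this imbalance about 16% of the time.

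**Step 3. All randomisations.** Simulation of eight groups of 60 under pure randomisation (400,000 draws):
- When a given technique contrast is itself significant at 5%, the eight-group test is significant in 23% of draws, so it misses about 77%.
- When the eight-group test is significant, 41% of draws show no significant main-effect contrast.

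Large imbalances are usually caught: if the underlying technique difference is 0.4 SD at N = 480, the power of the eight-group test is 91%.

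**Step 4. Consequence for a POST-only contrast at N = 480.** Simulation of no adjustment, the plan's rule and fixed adjustment (6,000 draws per correlation). Bias is the mean over draws with a technique-level imbalance of at least 0.18 SD.

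| Correlation | Bias, unadjusted | Bias, plan's rule | Bias, always adjusted | SD of estimate, plan's rule | SD of estimate, always adjusted |
|---|---|---|---|---|---|
| 0.3 | 0.061 | 0.045 | about 0 | 0.091 | 0.087 |
| 0.5 | 0.108 | 0.076 | about 0 | 0.092 | 0.081 |

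At correlation 0.1 simulation noise dominates, so the direct calculation is more useful. In draws with an imbalance of at least 0.18 SD, the mean imbalance is 0.214 SD. Counting flagged draws as zero, 0.161 SD remains unadjusted under the rule. Multiplying by the correlation gives:
- 0.1 × 0.161 = 0.016 SD;
- 0.3 × 0.161 = 0.048 SD;
- 0.5 × 0.161 = 0.080 SD.

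The last two agree with the table within simulation error. An imbalance of this size on a given technique occurs in about 5% of randomisations.

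The simulated type I error over all draws is between 4.8% and 5.9% for all three approaches and all three correlations. That is near 5%, with no excess for the rule.

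**Step 5. Change from PRE.** With complete data, the shift in a technique-by-time effect is the imbalance times the difference between the covariate's slopes at POST and PRE. For a 0.2 SD imbalance and equal outcome SDs:
- correlation 0.3 at both times: 0.2 × (0.3 − 0.3) = 0;
- 0.2 at PRE and 0.3 at POST: 0.2 × 0.1 = 0.02 SD.

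Drop-out makes the cancellation inexact.

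**The case against.** The strongest case for leaving the rule alone is that it does little harm here. Both candidate covariates and the trigger are named in advance, and the trigger uses baseline data only, so no result can steer the choice. Chance imbalance has random direction and ordinary standard errors already allow for it. The primary analysis concerns change and PRE is measured, so a stable age or gender effect largely cancels. All of this stands, and it limits the size of the point. It does not make the test a sensible way to choose covariates.

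Three stronger readings are tempting, and the documents do not support them.

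- **A bias of about a third of the target effect.** A reader could multiply a 0.2 SD imbalance by a correlation of 0.3 to get 0.06 SD, and divide by 0.19 to get 32%. That describes an unadjusted POST-only contrast, whereas the plan models repeated measures. The correlation is assumed. The article says only "we would like to be able to observe a small effect size of 0.19" and gives no metric, so dividing by it presumes SD units.
- **An inflated false-positive rate.** The simulations show none.
- **Missing data handled without age and gender.** The covariate rule concerns the analyses. The following paragraph plans multiple imputation and neither lists nor restricts the imputation variables. The text does not show that age and gender are left out, and this is detail that an article may leave to a fuller document.

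**Conclusion.** The point holds as a modest, well-defined weakness. The article fixes a rule under which chance decides whether age and gender enter the primary model, using a comparison that is insensitive to imbalance on a single technique.

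The trigger rates rest on an assumed 0.05 threshold. If no threshold is intended, the rule is looser still, because what counts as a difference is left to judgement. The bias and precision figures rest on assumed correlations and on a contrast at one time point. The lost precision is about 4% of the SD of the estimate at correlation 0.3 (0.091 to 0.087) and about 12% at 0.5 (0.092 to 0.081). For change from PRE the conditional bias is smaller, possibly near zero, and the precision gain should shrink for the same reason. The validity of the trial is not in question.

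**What to change.** Replace the conditional sentence with: *Age and sex will be included as covariates in the primary and secondary outcome models in every case.* State that baseline tests will not be used to select covariates.

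Baseline comparisons of the other variables may stay as descriptive input to the planned sensitivity analyses. Naming age and sex in the imputation model as well would be sensible, as a clarification and not as the correction of a stated error.

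The cost is one sentence and two degrees of freedom. Both variables are already among the demographic data collected, and the sample size does not change.

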## Aims and objectives

Our primary aim is to investigate which combination of behaviour-change techniques of an e- and m-health intervention in adults results in an optimal efficacy. We will explore the role of three behaviour-change techniques (i.e. action planning, coping planning and self-monitoring) on PA, SB and the attainment of self-formulated goals. We will apply an experimental approach and conduct a 2 x 2 x 2 factorial randomised trial using ‘MyPlan 2.0’, an e- and m-health intervention to increase PA and to reduce SB among adults.

Our second aim is to investigate the effect of the self-regulation techniques on mediating change-related determinants (i.e. self-efficacy, motivation, intention, action planning, coping planning, self-monitoring, risk perception and outcome expectancies) and to examine possible moderating effects of demographic variables. Hypotheses about mediation and moderation are informed by the HAPA [27, 39, 40], a self-regulation model that includes both pre-intentional as well as post-intentional determinants of behaviour change.

Our third aim is to investigate whether our intervention is effective for particular groups of participants. According to the HAPA model, individuals can be divided into three groups, based on their ‘mindset’ regarding behaviour change. The first group or ‘pre-intenders’ consists of individuals that have not yet formed an intention. The second group or ‘intenders’ have formed an intention to change their behaviour, but they do not yet perform the action itself regularly. The third group or ‘actors’ already perform the action for which they previously formed an intention. Interventions can be tailored upon these different mindsets, hence targeting mostly pre-intentional or post-intentional determinants. Because our intervention focusses on bridging the intention-behaviour gap, we expect that our intervention works better for intenders than for pre-intenders and for actors.

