**Fig. 3 Fig3:**
[figure not shown]
Standard Protocol Items: Recommendations for Interventional Trials (SPIRIT) Figure. The figure shows the phases of the trial and the overview of variables measured at five time points

PA and SB, the primary outcomes, will be assessed via self-report measures. The IPAQ [61] will be used to measure self-reported total PA and moderate-to-vigorous PA across different domains (i.e. work, home, leisure time, transport). A 7-day sedentary behaviour self-report questionnaire (SIT-Q-7d) [62] will be used to measure domain-specific total sedentary time in five domains (meals, transportation, occupation, non-occupational screen time and other sedentary time). Both questionnaires have shown fair to good reliability and validity [61, 62]. Furthermore, users will report weekly to what extent they achieved their PA or SB goal (secondary outcome measure). After seeing the goal(s) they set the week before, the following question will be asked: ‘Did you reached your goal(s)?’: ‘Yes’, ‘No’ or ‘A little’.

To evaluate our second aim of the intervention, psychosocial determinants of behaviour (i.e. self-efficacy, motivation, outcome expectancies, risk perception, intention and the degree to which action planning, coping planning, self-monitoring is used in daily life) will be measured via a set of 32 items (i.e. at least three items per determinant). This set was iteratively developed and validated by an expert panel, using (1) cognitive interviewing [63, 64] and (2) a procedure for content validity which was based on the method of Johnston et al. (2014) [65]. In a first step a large pool of items were created measuring the personal determinants based upon the HAPA model [27]. Next, 11 experts in the field of self-regulation theory (which the determinants were based on) rated to what extent each item measured each construct of the HAPA model. Also feedback on the formulation was provided, and some items were reworded. Finally, a team of three researchers selected the best scoring items.

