To evaluate the primary aim of the intervention, PA and SB will be analysed in one statistical analysis. The scores of PA and SB will be standardised (z-score) in order to obtain a common metric. For PA, the mean and SD of the population will be based on self-report IPAQ data self-report IPAQ data from Belgian adults (m_totalPA_ = 831.5 min/week, SD_totalPA_ = 579.8; m_MVPA_ = 459.9 min/week, SD_MVPA_ = 407.2 min/week) [77]. For SB, the mean and standard deviation of the population will be based on self-report SIT-Q-7d data from Belgian adults (m_totalSB_ = 9,57 h/day, SD_totalSB_ = 3,20 h/day) [78]. The z-scores for SB will be multiplied by − 1. That way the amount of healthy behaviour is reflected in positive scores. Mixed models (two levels: repeated measures clustered within participants) will be performed using the ‘lme4-package’ [79] to investigate the effect of the (combination) of the three behaviour-change techniques (i.e. action planning, coping planning and self-monitoring) on behaviour change [80]. The participants’ choice of target behaviour (i.e. PA or SB) will be included in the analysis as a moderator. Furthermore, to evaluate our secondary outcome, logistic regression analyses will be used to investigate whether the process on goal achievement has an influence on the primary outcome.

To evaluate the secondary aim of the intervention, PA and SB will be analysed both together for analysing the mediating effect of personal determinants. This because all participants filled out one version of the personal determinants (i.e. the version focussing on PA or the version focussing on SB). These outcome variables will be considered as personal determinants regarding the chosen health behaviour rather than personal determinants regarding increasing PA or decreasing SB. Mediating effects of the personal determinants of behaviour will be investigated using structural equation modelling [81]. Next, moderating effects of demographic variables will be identified via interaction terms by including them as an extra between factor in the analyses.

To evaluate the third aim of the intervention, three groups of participants will be identified based on their ‘mindset’ regarding behaviour change: ‘pre-intenders’, ‘intenders’ and ‘actors’. This will be based on their answer on the personal determinant ‘intention to change’. The moderating effect will be identified via interaction terms by also including them as an extra between factor in the analyses.

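### The analysis stated for goal attainment, the secondary outcome, makes it a predictor of the primary outcome, names no randomised technique, and does not fit the scale of the response

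*Protocol article*

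**What the plan says.** Under Aims and objectives, the primary aim includes the role of the three techniques "on PA, SB and the attainment of self-formulated goals". Goal attainment is therefore something the techniques are meant to change.

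Under Measurements, physical activity (PA) and sedentary behaviour (SB) are the primary outcomes. For goal attainment the text is that "users will report weekly to what extent they achieved their PA or SB goal (secondary outcome measure"). The response options are "Yes’, ‘No’ or ‘A little".

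Under Data management and statistical analysis, PA and SB are put on one scale: "The scores of PA and SB will be standardised (z-score) in order to obtain a common metric". Two-level mixed models are then used "to investigate the effect of the (combination) of the three behaviour-change techniques" on behaviour change. The same paragraph closes with the secondary outcome, for which "logistic regression analyses will be used to investigate whether the process on goal achievement has an influence on the primary outcome".

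**The concern.** The aim asks whether the randomised techniques change goal attainment. The analysis sentence asks whether goal attainment changes the primary outcome. These are different questions, and only the first is a randomised comparison.

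Goal attainment is reported during the intervention, after allocation. Participants who reach their goals may differ from those who do not in motivation, time or health, so its association with PA or SB is open to confounding whatever group they were allocated to. An analyst who follows the sentence would report that association in place of the secondary result, and the question in the aim would go unanswered. The Discussion presents the experimental design, which separates the effects of the individual techniques, as a main strength of the trial. For this outcome the stated analysis does not use that strength.

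The model is also at odds with the variable. Logistic regression needs a categorical response, and the response named in the sentence is continuous.

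**Working it through.** No figure in the article bears on this point, so the check sets the texts side by side.

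**Step 1: role of each variable.**

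| Place in the article | Goal attainment | PA/SB | Three techniques |
|---|---|---|---|
| Aims and objectives | response | response | explanatory |
| Measurements | secondary outcome | primary outcomes | not mentioned |
| Statistical analysis, mixed models | absent | response | explanatory |
| Statistical analysis, logistic regression | explanatory | response | absent |

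The last row conflicts with the first: goal attainment has changed sides and the randomised factors have gone.

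**Step 2: is the effect on goal attainment tested elsewhere?** The remaining analyses in the same section are these:

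- Second aim: "Mediating effects of the personal determinants of behaviour will be investigated using structural equation modelling". The determinants listed under Aims and objectives and under Measurements do not include goal attainment.
- Moderation by demographic variables: interaction terms added to the analyses, with no separate model for goal attainment.
- Third aim: moderation by mindset group, handled in the same way.

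None has goal attainment as the response and the techniques as factors.

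**Step 3: does the model fit under either reading?**

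- *Literal reading (PA/SB as response).* The response is a z-score. No cut-off that would make it categorical is stated, so logistic regression cannot be applied to it as described.
- *Reversed reading (goal attainment as response).* A model of the logistic family is then suitable. The item has three ordered levels and is asked weekly, so the model must accommodate both. The sentence still does not name the techniques.

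**Step 4: timing.** Under Data collection procedures, allocation follows completion of the pre-test measurement. The weekly goal reports come later, in the follow-up sessions. Goal attainment is therefore a post-randomisation variable, and using it as a predictor gives a non-randomised comparison.

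**The case against.** The strongest reply is that this is a slip of language. The sentence opens by saying that it evaluates the secondary outcome, and it names logistic regression, which suits a categorical goal item and not a z-score. Its wording is awkward, and there are similar slips elsewhere in the article. The authors may well have meant goal attainment as the response. A statistical analysis plan, not shown, may contain the right model. The Abstract states its aim in terms of PA, SB and related determinants, without goal attainment. The allocation and the weekly reports are collected in any case, so the comparison stays possible.

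Much of this stands, and it limits the severity. It does not remove the point. The article does not merely leave out detail: it states an analysis that conflicts with its own aim and with the scale of its own variables. A plan that copied the sentence would inherit the conflict.

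Three stronger readings are tempting but are not supported:

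- *A reader might infer inflated error rates from treating weekly answers as independent.* The article does not say that the answers will be pooled or that clustering will be ignored, and it gives no within-person correlation. The same paragraph specifies mixed models for repeated measures of the primary outcome. Any such figure would measure a different, unstated analysis.
- *A reader might infer that the answer A little will be discarded.* The article says only logistic regression, a term that can cover ordinal and multinomial forms. Dichotomising would merge a category and need not drop it.
- *A reader might infer that the control group has no goal to report on*, because Study design gives it only tailored feedback, information and tips. The Abstract describes all versions as directed at self-formulated goals. The website flow in Figs. 1 and 2, which might settle where goals are set, is not shown. The contradiction cannot be established.

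**Conclusion.** The point holds as an inconsistency in the stated analysis. Read literally, the sentence uses a post-randomisation variable as predictor, leaves out the randomised techniques and applies a logistic model to a continuous response. It contradicts the aim, and the article describes no other test of the techniques on goal attainment.

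Its size is one designated secondary outcome without a described randomised comparison. No numerical magnitude can be taken from the document. A reader might infer that the comparison is lost or will never be made. The documents support only that this article does not describe it: the data would allow it, the sentence may be a wording error, and an analysis plan may exist.

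Severity is should-fix, because the outcome is secondary and the mixed model for PA and SB, which does include the techniques, is unaffected. The verdict assumes only that the sentence means what it says. If it was meant the other way round, it still has to be rewritten to agree with Aims and objectives and with Measurements.

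**What to change.** Replace the sentence with a short paragraph that does the following:

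- Makes weekly goal attainment the dependent variable, analysed by randomised group.
- Includes the three techniques and their two-way interactions as fixed effects. The Discussion says that main effects and two-way interactions are the effects of interest.
- Includes chosen behaviour (PA or SB) as a moderator, as in the primary model.
- Uses a logistic-type model suited to three ordered levels repeated within participants, for example a cumulative-logit mixed model with a participant random intercept. This is one valid choice among several. If a binary form is preferred, state how the middle answer is coded and keep the participant effect.
- Labels any association of goal attainment with PA or SB as exploratory and non-randomised, and fits it with a linear (mixed) model, because the response is a z-score.

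The cost is one paragraph of text and a standard R package for ordinal mixed models. No new data are needed. The article says that analysis follows completion of data collection, so the change can be made and recorded as a protocol modification before the outcome is analysed.
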